## Abstract

**Introduction:**

Early recognition and appropriate management of paediatric sepsis are known to improve outcomes. A previous system’s biology investigation of the systemic immune response in neonates to sepsis identified immune and metabolic markers that showed high accuracy for detecting bacterial infection. Further gene expression markers have also been reported previously in the paediatric age group for discriminating sepsis from control cases. More recently, specific gene signatures were identified to discriminate between COVID-19 and its associated inflammatory sequelae. Through the current prospective cohort study, we aim to evaluate immune and metabolic blood markers which discriminate between sepses (including COVID-19) from other acute illnesses in critically unwell children and young persons, up to 18 years of age.

**Methods and analysis:**

We describe a prospective cohort study for comparing the immune and metabolic whole-blood markers in patients with sepsis, COVID-19 and other illnesses. Clinical phenotyping and blood culture test results will provide a reference standard to evaluate the performance of blood markers from the research sample analysis. Serial sampling of whole blood (50 μL each) will be collected from children admitted to intensive care and with an acute illness to follow time dependent changes in biomarkers. An integrated lipidomics and RNASeq transcriptomics analyses will be conducted to evaluate immune-metabolic networks that discriminate sepsis and COVID-19 from other acute illnesses. This study received approval for deferred consent.

**Ethics and dissemination:**

The study has received research ethics committee approval from the Yorkshire and Humber Leeds West Research Ethics Committee 2 (reference 20/YH/0214; IRAS reference 250612). Submission of study results for publication will involve making available all anonymised primary and processed data on public repository sites.

**Trial registration number:**

NCT04904523.

Strengths and limitations of this studyMultimodal investigation of molecular biomarkers for the early diagnosis of paediatric sepsis using a minimally invasive low blood volume.Identification of host response molecular patterns associated with various infections (bacterial, viral and fungal).Immunophenotyping, immunoassays, lipidomics and functional analysis will be performed during the hospital journey and in cases of suspected sepsis to investigate time-dependent changes in biomarkers of sepsis.Potential selection bias towards younger cases.Single site observational study.

## Introduction

Sepsis is a global health problem affecting all age groups. A systematic review of published literature from 1979 to 2016 was carried out to estimate population-based sepsis incidence in neonates and children. Reports from 15 studies in 12 countries showed an aggregate estimate of 48 (95% CI 27 to 86) sepsis cases and 22 (95% CI 14 to 33) severe sepsis cases in children per 100 000 person-years. The population-level estimate for neonatal sepsis was 2202 (95% CI 1099 to 4360) per 100 000 livebirths, with mortality between 11% and 19%. Extrapolating on a global scale gave an estimated incidence of approximately 3 million cases of sepsis in neonates and 1.2 million cases in children annually. Mortality ranged from 1% to 5% for sepsis and 9% to 20% for severe sepsis.^1^

### Definition of sepsis in children

At present, sepsis is defined in adults as life-threatening organ dysfunction resulting from a dysregulated host response to infection.^2^ This definition has removed the terms ‘systemic inflammatory response syndrome’ (SIRS) and ‘severe sepsis’ found in previous definitions and highlights organ dysfunction for clinical management. In children, the existing surviving sepsis consensus conference definition of sepsis based on the criteria for SIRS in the presence of confirmed or suspected infection is still used for identification of sepsis and clinical research.^3^ The recently updated guidance for the management of sepsis in children (2020) recognises the clinical heterogeneity of this illness in children, accounting for life-threatening organ dysfunction.^4^ A revised definition of sepsis by the paediatric sepsis definition task force is awaited.^5^ Recently, we put forward a setpoint mechanism for understanding sepsis. This suggests that dysregulation of the host response to infection in sepsis is explainable by regulatory shifts in homeostasis setpoints. This is due to negative and positive feedback changes in the concerted behaviour of multiple (immune, metabolic and neuronal) systems in response to infection. We hypothesise that infants and children have age-dependent metabolic demands and a developing immune setpoint that increases the risk of sepsis.^6^ Sepsis can arise from any type of infection—bacterial, viral, fungal or parasitic.^4^ Even though less common in children, COVID-19 can be associated with severe illness. History of infection and age-dependent changes in the immune system give rise to subtle but important differences in response to SARS-CoV-2 infection in children when compared with adults. In the early life and younger years, the innate response is a dominant feature of the immune response to infection. In the case of SARS-CoV-2 infection, children are known to mount a stronger and more vigorous interferon (IFN) antiviral response than adults, curtailing viral replication at an early stage of infection.^7^

### Biomarkers in sepsis

Several host inflammatory biomarkers have been suggested to improve the ability for early recognition of sepsis. These include C reactive protein, procalcitonin, interleukin 8, soluble CD14 (presenilin) and triggering receptor expressed on myeloid cells that have all been evaluated without conclusive results.^8^ It is important to recognise that sepsis is a complex pathophysiological process comprising an immune response which interacts with the body’s metabolic and physiologic functions. A profile of multiple markers capturing the complexity of the pathophysiological response would be better than an individual marker to detect and study the disease process.^9^ In neonatal sepsis, it has been shown that the inclusion of metabolic markers as well as adaptive immune responses with innate immune signal changes, increased the accuracy for early recognition of sepsis.^10^ These complex molecular changes during sepsis correlate with altered gene expression^11^ and in some infectious illnesses, there was a unique signature alteration in gene expression with a demonstrable value in understanding pathogenicity.^12–14^ Gene expression markers have been evaluated to identify bacterial infections in febrile children^15^ and differences in transcriptomic profiles in blood have been used to discriminate clinical phenotypes and subgroups of sepsis.^16 17^

### COVID-19 in children and young people admitted to paediatric intensive care

Infection with SARS-CoV-2 is mild or asymptomatic in the majority of children.^18 19^ The proportion of children presenting to the hospital who have severe COVID-19 and require admission to intensive care has been variable ranging from 1.75% in China^20^ to a higher rate of 9.7%–28% in the western world.^21–23^ The clinical risk factors for severe COVID-19 in children have been reported to be age over 10 years, black and Asian ethnic groups, comorbidities and obesity.^23 24^ The difference in the severity of COVID-19 in children, when compared with adults and the elderly, has been studied extensively. Various factors to explain this difference have been reported and include vasculopathy, the density of ACE 2 receptors, age-based differences in coagulation profiles and immune responses,^25^ and heightened antiviral IFN response.^7^ Paediatric inflammatory multisystem syndrome temporally related to SARS-CoV-2 (PIMS-TS) also called multisystem inflammatory syndrome in children is a hyperinflammatory syndrome seen in some children following contact with SARS-CoV-2. Two phenotypes have been described—high fevers with severe gastrointestinal symptoms; and shock with myocardial dysfunction and Kawasaki disease-like clinical features. Research to evaluate the pathophysiology of PIMS-TS reported an abnormal immune response mediated by superantigen activity of the SARS-CoV-2 S glycoprotein.^26^ It has also been associated with immune markers related to endothelial dysfunction in children.^27^ Through this study, we hope to compare immune responses in children with COVID-19, PIMS-TS and sepsis.

### Study methods for molecular and cellular analysis

The studies so far have been restricted to using transcriptomic analysis for an observational case–control methodology to identify differentially expressed genes in children with sepsis (cases) when compared with children without an acute illness (controls). The evaluation of differentially expressed genes in a particular illness, when compared with healthy controls, helps in understanding the biological pathways and pathophysiology of the disease processes. However, the use of healthy controls in studies aiming to identify gene expression markers that discriminate a particular disease from other illnesses may lead to spectrum bias and fail to account for time-resolved differences.^28^ Further, the use of other modal data inclusive of metabolites, in particular lipids, proteomic, cellular and clinical observations allow for a more complete picture of the underlying pathophysiology and diagnostic algorithm development. We propose a prospective cohort methodology to investigate the differentially expressed genes over time in children with sepsis and other acute illnesses.

## Methods

### Hypothesis and specific aims

A neonatal sepsis classifier integrating immune and metabolic pathways was able to discriminate neonates with bacterial infections and sepsis with high accuracy.^10^ We hypothesise that the integrative tripartite immune-metabolic pathways represented by differentially expressed genes between sepsis and other illnesses would discriminate bacterial infection causes of sepsis from COVID-19 illness and other acute non-infectious illnesses. The immune-metabolic pathways vary between different age groups in children under 18 years. Our specific aims include:

Compare immune and metabolic markers, which discriminate sepsis and COVID-19 from other acute non-infectious illnesses in children admitted to paediatric intensive care unit (PICU).Investigate the evolution of immune responses in children with sepsis and COVID-19 using serial samples.Evaluate the utility of gene expression markers to discriminate heterogeneous subgroups of sepsis and other critical illnesses with the help of deep clinical phenotyping.Understand physiological processes associated with COVID-19 and PIMS-TS and how they differ from bacterial sepsis aetiology.Explore age-dependent differences in systemic host response and determine whether these differences are associated with the risk of disease severity to infection.

We plan to explore the feasibility of objectively defining the balance between immune tolerance and resistance in general, as well as in different paediatric age groups. This is through investigating pathway biology response to sepsis and multiomic analyses.

This is a prospective cohort study with a nested case–control analysis. The start date was 30 June 2020 and the proposed end date is 01 June 2023.

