As the revisions to the definition of sepsis are pending, clinical phenotyping will be broadly based on the surviving sepsis consensus definition (2005). Patients will be included if they meet two or more criteria of SIRS, with at least one criterion related to white cell count or temperature, and with confirmed or strongly suspected to have an infection.^3^ There have been algorithms used previously to identify bacterial infections.^15 30^ In this study, we plan to evaluate sepsis due to any aetiology including fungal or viral infections. The clinical phenotyping will aid in categorising patients into descriptive clinical clusters, which we believe would have more utility in studying differences in immune-metabolic biological pathways between sepses due to viral, bacterial or fungal sepsis or where there is no microbiological agent identified. The process aims to report those cases as sepsis, which may deviate from the 2005 consensus definition, but have strongly suspected or confirmed infection and life-threatening organ dysfunction as described in the latest surviving sepsis consensus guidance statement.^4^ In addition, we can study the differences in sepsis as a whole in comparison with other acute illnesses. In those patients with confirmed infections and who do not meet the SIRS criteria for sepsis, deep clinical phenotyping will help us in evaluating the immune and metabolic markers based on patient outcomes such as severity of illness and organ dysfunction.

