### Data processing and analysis

Paired-end reads from RNAseq Illumina sequencing will be trimmed and processed for quality control,^35 36^ before mapping to the human genome using Spliced Transcripts Alignment to a Reference.^37^ Once we have read counts per gene/transcript, we plan to use R Language and Environment for Statistical Computing^38^ followed by quality control and data processing using Bioconductor packages.^39^ A per-gene hypothesis of differential average expression will be tested using a negative binomial generalised linear model—DESeq2 package and resulting p values will be controlled for multiple testing using the Benjamini-Hochberg method.^40^ For classification, a variety of machine learning and statistical pathway biology approaches, as described in Smith *et al*,^10^ will be used. Pathway analyses will be carried out stepwise using a pathway biology approach, becoming more focused. For metabolomic and proteomic data, absolute concentrations (determined by LC-MS/MS) of analytes in extracts from blood samples will apply validated tools such as MetaboAnalyst V.4.0.^41^ Further multivariate statistical testing (Principal Component Analysis, Partial Least Squares Discriminant Analysis, Random Forest and Analysis of Variance) using group assignment derived from clinical phenotyping (types of sepsis and between sepsis and non-septic controls) will also be used to determine metabolites or proteins that are significantly different in abundance between clinical phenotypes. Single-cell analyses (CITE-Seq) using surface protein and RNA libraries (10× Genomics) and next-generation sequencing will be multiplexed by cell ‘hashing’.^42^ Demultiplexed sequencing data will be aligned to the reference transcriptome using CellRanger (10× Genomics) and the number of unique molecular identifiers per cell will be quantified. Computational analyses and quality control will be performed using R packages including Seurat to integrate hashtag, protein and RNA libraries while also enabling demultiplexing of donors, doublet detection and cell clustering.^43^

For the final pathway biomarker assessment of the predictive success of the model, Receiver Operator Characteristics will be applied.

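### Aim 1 limits the comparator for sepsis to non-infectious illness, unlike the abstract and analysis section, and no stated contrast isolates sepsis from non-septic infection of the same type

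*Protocol article*

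**What the plan says.** The protocol article gives three different comparators for its central contrast.

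- **Aim 1** (Hypothesis and specific aims): "Compare immune and metabolic markers, which discriminate sepsis and COVID-19 from other acute non-infectious illnesses in children admitted to paediatric intensive care unit (PICU". The comparator is non-infectious illness.
- **Abstract, Introduction**: the study seeks markers "which discriminate between sepses (including COVID-19) from other acute illnesses in critically unwell children and young persons". The comparator is any other acute illness.
- **Data processing and analysis**: the multivariate testing of metabolites and proteins groups children by "types of sepsis and between sepsis and non-septic controls". The comparator is every child without sepsis. The sentence on differential gene expression names no groups.

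Infected children without sepsis are in the cohort. The Patient/family journey section makes any child admitted to the critical care unit with an acute infectious or non-infectious illness eligible. Case definitions and group stratification criteria expects some who are infected but not septic: "In those patients with confirmed infections and who do not meet the SIRS criteria for sepsis, deep clinical phenotyping will help us in evaluating" their markers by outcomes such as severity and organ dysfunction. That sentence does not place them in a comparator group.

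**The concern.** Under Case definitions, sepsis is essentially SIRS plus confirmed or strongly suspected infection. Against trauma and other sterile illness, infection is present on one side and absent on the other. A marker that responds to infection, and says nothing about whether the child is septic, would therefore succeed in Aim 1. The children who could expose this are already enrolled but fall outside Aim 1's contrast.

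The infectious comparators named elsewhere help only in part. COVID-19, PIMS-TS and viral infection differ from bacterial sepsis in cause as well as in septic status, so a marker of bacterial infection would separate those groups too. The risk is practical: the abstract describes the earlier neonatal markers as accurate for detecting bacterial infection, and the analysis section plans to reuse that work's classification approaches. At stake is whether a reported sepsis marker has been shown to identify sepsis or only its infectious cause.

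**Working it through.** **1. The plan's own figure.** Sample size calculation gives about 20 samples per group for a twofold change, with a coefficient of variability of 0.6, power 0.8 and α 0.01. The negative binomial formula is

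n per group = 2 × (z₁₋α/₂ + z_power)² × (1/μ + CV²) / (ln FC)²

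Two-sided, with μ the mean read count per gene (not given, so assumed):

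- 2 × (2.576 + 0.842)² / (ln 2)² ≈ 48.6
- μ = 20: 48.6 × (0.05 + 0.36) = 19.9
- μ = 50: 48.6 × (0.02 + 0.36) = 18.5
- μ very large: 48.6 × 0.36 = 17.5

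The figure reproduces and does not depend on the choice of comparator. It matters here only as the group size that an added contrast would need.

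**2. Would a marker of bacterial infection alone pass each stated contrast as a marker of bacterial sepsis?**

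| Place | Contrast | Would it pass? |
|---|---|---|
| Aim 1 (its bacterial sepsis cases) | Sepsis and COVID-19 v non-infectious illness | Yes |
| Hypothesis | Bacterial sepsis v COVID-19 and non-infectious illness | Yes |
| Aim 4 | COVID-19 and PIMS-TS v bacterial sepsis | Yes |
| Discussion | Confirmed sepsis v confirmed viral infection, COVID-19 or PIMS-TS | Yes, for bacterial sepsis |
| Case definitions (optional) | Sepsis as a whole v other acute illness | Weakened, since infected non-septic children are pooled in but not isolated |
| Data processing and analysis | Sepsis v non-septic controls | Weakened, for the same reason |

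Aim 3 refers to subgroups of sepsis and other critical illnesses, without a specific contrast. No place names bacterial sepsis against bacterial infection without sepsis.

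**3. Illustration with assumed rates.** Suppose a marker is positive in 90% of children with bacterial infection and in 10% of all others, whether septic or not. Take bacterial sepsis as the case group, and let q be the share of the comparator group with bacterial infection.

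- Specificity = (1 − q) × 0.90 + q × 0.10
- AUC of a binary marker = (sensitivity + specificity) / 2, with sensitivity 0.90

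| Comparator | q | Specificity | AUC |
|---|---|---|---|
| Non-infectious or viral illness | 0 | 0.90 | 0.90 |
| All non-septic | 0.2 | 0.74 | 0.82 |
| All non-septic | 0.4 | 0.58 | 0.74 |
| All non-septic | 0.6 | 0.42 | 0.66 |
| Non-septic bacterial infection | 1 | 0.10 | 0.50 |

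**4. Could the missing contrast be supported?** The plan expects about 25 septic children among 250, leaving 225. A group of 20 infected non-septic children would need 20/225 = 8.9% of those. The documents do not give this share. With 25 against 20, a continuous marker with no discrimination has a standard error for the AUC of √[(25 + 20 + 1)/(12 × 25 × 20)] = 0.088. The 95% interval around 0.50 is then about 0.33 to 0.67, which is wide.

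**The case against.** The strongest reply is that Aim 1 is one of five aims and the rest of the plan is wider. Most of this stands, and it rules out several stronger readings.

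- **That the hypothesis has the same restriction.** It does not. It expects the pathways "would discriminate bacterial infection causes of sepsis from COVID-19 illness and other acute non-infectious illnesses", and COVID-19 is an infection, so a marker of infection in general would fail. Its genes are those "represented by differentially expressed genes between sepsis and other illnesses", which is not limited to non-infectious illness.
- **That infected non-septic children are excluded from every comparison.** The documents do not say so. Case definitions also allows sepsis as a whole to be compared with other acute illness, and the evaluation by outcome is not stated to be exclusive. The Discussion's list of contrasts is given as examples.
- **That the ROC analysis will use Aim 1's comparator.** The analysis section names no comparator for it.
- **That this is the bias which the article itself warns of.** Its remark that a design "may lead to spectrum bias and fail to account for time-resolved differences" concerns healthy controls. Aim 1 uses acutely ill children, which is an improvement. The present problem is related but different.

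It is also fair that the illustration is true by construction, because the marker is defined to carry no information on sepsis. The number of infected non-septic children is unstated and may be small: children with infection and life-threatening organ dysfunction can be classed as septic even when they deviate from the 2005 definition.

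The reply does not remove the difference in wording between Aim 1 and the abstract and analysis section, or the absence of any contrast within infection of one type. The first is a discrepancy in the text, not detail left to an analysis plan.

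**Conclusion.** The point holds for Aim 1 and for one missing contrast, and the plan should be changed on both. Aim 1's comparator is narrower than those of the abstract and the analysis section. Contrasts elsewhere would reveal a marker of infection in general, but none isolates sepsis from non-septic infection of the same type.

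The size cannot be estimated from the documents. The AUCs of 0.90, 0.82 to 0.66 and 0.50 rest on assumed positivity of 90% and 10% and an assumed share of 20% to 60%. They show how far apart the answers can lie for one marker, and they do not predict this study's results. A reader might infer that the study will produce a classifier that fails in infected children. The documents do not support that, since the wider comparisons may be run and the eventual marker is unknown.

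**What to change.** Reword Aim 1 so that the comparator for sepsis is all non-septic acutely ill children, in line with the abstract and the analysis section. Report the differential expression and ROC results for sepsis:

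1. against all non-septic children;
2. against non-infectious illness;
3. against infection without sepsis, split into bacterial and viral where numbers allow.

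Give confidence intervals throughout, and state how many infected non-septic children there are. Where the within-infected contrast is not informative, say that the marker has not been shown to separate sepsis from infection. Discrimination within infected children should not be made a condition for any claim about sepsis, because about 25 septic cases may be too few to settle it.

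The change uses children already enrolled and needs no further samples. The AUC will probably be lower than against non-infectious illness alone, and the within-infected estimate will be imprecise.
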